## Abstract

**Abstract:**

**Introduction:**

Australian studies investigating parental factors often lack meaningful inclusion of Aboriginal and Torres Strait Islander families, limiting our understanding of current influences on positive developmental trajectories within communities. There is growing recognition of the need for culturally safe and responsive longitudinal research that is co-designed and co-led by the community for the community. An Indigenous-led birth cohort study of Aboriginal and Torres Strait Islander families in Queensland, Australia, has therefore been developed to better understand health across generations.

**Methods and analysis:**

The Strong Families Study is a co-designed prospective longitudinal birth cohort study that will follow 400 Indigenous families in Queensland from pregnancy until the child reaches 5 years of age. Eligible participants include pregnant individuals (<28 weeks’ gestation) whose children may identify as Aboriginal and/or Torres Strait Islander, along with their partners (if applicable). Data will be collected at multiple timepoints: during gestation, at delivery, postpartum, every 6 months until the child is 36 months (corrected age, CA) and annually until age 5 years. These will be collected by Aboriginal health workers using validated and culturally appropriate tools across different health themes. The study will incorporate health literacy throughout, as well as referrals to two nested family support programmes to support families and assist with the developmental outcomes of their children when and if required. Effects across health themes will be analysed with a focus on strengths, positive trajectories and holistic well-being of Indigenous families, moving beyond deficit-based narratives.

**Ethics and dissemination:**

This study was approved by the Mater Misericordiae Ltd Human Research Ethics Committee (HREC/MML/105191) and ratified by the University of Queensland Human Research Ethics Committee (2025/HE001924). Endorsement letters were secured from partner services at each study site. Findings will be shared with partnering hospitals and funding bodies at conferences and through reports and peer-reviewed publications.

STRENGTHS AND LIMITATIONS OF THIS STUDYThis co-designed birth cohort study integrates Indigenous knowledge systems into its design and uses strength-based approaches that emphasise positive trajectories within Indigenous families.The inclusion of both partners in the birth cohort study, as well as the collection of biological samples from all participants, offers novel insights into family health determinants.Multiple in-person visits, from pregnancy through birth and childhood, may be burdensome for participants and increase the risk of attrition.Restricting enrolment to individuals <28 weeks’ gestation may limit generalisability of findings.

## Introduction

 Globally, Indigenous peoples constitute over 6% of the population, with an estimated 476.6 million individuals across all regions.^1^ For millennia, these populations have recognised the profound impact of past generations on shaping the life experiences of the present. This perspective aligns with the Developmental Origins of Health and Disease (DOHaD) framework, which emphasises the role of early-life environmental factors in influencing children’s development, risk factors for disease and their long-term health throughout their lifespan.^2^ The understanding of DOHaD is particularly evident in Australia, where Aboriginal and Torres Strait Islander (hereafter respectfully ‘Indigenous’) people have the oldest continuing culture in the world, with Aboriginal knowledge systems having survived for over 60 000 years.^3^ As such, both the strength of Indigenous peoples and their cultural traditions have enabled them to persist and rise through the lasting impacts of colonisation. The maintenance of strong and cohesive identity and cultural practices including the centrality of country, community and family, underpinned by self-determination, has been identified as positively impacting the health and well-being of Indigenous peoples.^4^ These cultural foundations promote resilience and cultural continuity, contributing to positive outcomes for Indigenous families and the broader well-being of communities. Among Indigenous peoples worldwide, the concept of health is characterised by a holistic framework that integrates distinct yet interconnected dimensions.^5^ In the Australian context, Indigenous people define health as encompassing the physical, spiritual, cultural and social well-being of both individuals and their communities.^6^

The period of time from conception to age 5, being the first 2000 days of a child’s life, represents a critical developmental window which is a key focus of the DOHaD hypothesis. During this time, children undergo significant cognitive, social, emotional and physical growth, and their early experiences have long-lasting impacts on future health and well-being.^7^ The first 2000 days are increasingly recognised in academic, policy and mainstream health literature as a pivotal period that influences lifelong outcomes.^8^,^11^ Such research consistently demonstrates that early-life interventions and supports during this period are central to promoting positive parent-child relationships and developmental outcomes, particularly for populations that continue to experience the effects of colonisation. Given the influence of early experiences, exploring strategies and interventions to support children during the first 2000 days is critical for ensuring better health and developmental trajectories for future generations.

Among the limited research available, several key longitudinal studies have followed the health and development of Indigenous mothers and children in Australia. The Aboriginal Birth Cohort study (n=686 Aboriginal maternal-child pairs) in the Northern Territory is the largest and longest running of its kind.^12^ Other notable studies include the Gudaga Study^13^ in urban Sydney, which followed mother-infant pairs (n=155) through the first year; the Gomeroi Gaaynngal Study^14^ in rural and regional New South Wales, tracking participants from pregnancy through childhood (n=110 mother-infant dyads); and the PANDORA Study,^15^ which examines outcomes for Indigenous women (n=542), particularly those with diabetes during pregnancy in the Northern Territory. Despite these efforts, there are currently no birth cohort studies involving Australian Indigenous families that have research priorities and methodologies co-designed in partnership with Indigenous community members. Furthermore, to our knowledge, no existing birth cohort studies have actively included both Aboriginal and Torres Strait Islander fathers or second parents in their design and data collection.

Co-design underscores the importance of collaborating with key stakeholders through capability building, sharing decision-making, and the development of equitable, sustained partnerships.^16 17^ Co-design values consumer-driven research and engagement throughout all stages of the research process, using Aboriginal Participatory Action Research to ensure Indigenous voices are central and the study remains relevant and aligns with community priorities and needs.^17^,^20^ The integration of an Indigenous lens within these processes facilitates the recognition and integration of Indigenous knowledge systems and the opportunity for cultural considerations that have historically been overlooked in previous policies and mainstream research.^21^ Furthermore, such approaches can counter the pervasive deficit discourse research relating to Indigenous health and well-being, which are often negative and disempowering.^22 23^ By using Indigenous voices and lived experiences, co-design highlights the strengths and resilience of Indigenous peoples, framing these as essential pathways to self-determination and sovereignty rights.^24 25^ This co-design approach ensures the development and application of culturally sensitive methodologies that are more likely to be valued by the community they aim to serve.^18^ Overall, a co-design process underpins ethical reciprocal research, emphasising empowerment and equity to ensure meaningful, sustainable and beneficial outcomes for the community.

This paper describes the research protocol and methodology for The Strong Families Study, a co-designed, Indigenous-led, prospective longitudinal study of Indigenous families in Queensland, Australia. This birth cohort study aims to examine the perinatal strengths and risk factors among reproductive-aged Indigenous parents. Specifically, it seeks to explore associations between these parental strengths and potential risk factors and (1) maternal pregnancy outcomes, (2) neonatal and birth outcomes and (3) early childhood developmental outcomes, with the overarching goal of informing evidence-based policy and practice change. Families will be followed at multiple time points, throughout pregnancy and early childhood.

This study will be the first of its kind in Queensland, focusing on the needs of Aboriginal and Torres Strait Islander families, inclusive of both partners, particularly in the first 2000 days of a child’s life. This will be significant as Queensland has the second highest population of Indigenous people in Australia.^26^ Additionally, the study will incorporate two nested family support programmes that can support families going forward. The first programme, PACT Online,^27^ offers parents the opportunity to self-refer at any time to an online support programme grounded in acceptance and commitment therapy (ACT). The second, the Learning through Everyday Activities with Parents Study (LEAP), will establish a referral pathway for infants identified as having a higher chance of neurodevelopmental disabilities and their families.^28 29^

## Methods and analysis

### Study design and setting

The Strong Families Study (SFS) will be a longitudinal birth cohort study, with nested family support programmes designed to follow 400 Indigenous families in Queensland, Australia, from pregnancy (commencing in mid-2026) through to the child’s fifth year of life. Eligible participants will be assessed at multiple time points from pregnancy through early childhood. Comprehensive measurements and data collection, including biological samples, will be undertaken throughout the study. The measures will encompass a range of health-related themes, gathered from all participating family members.

The study will be conducted as a teletrial model across multiple sites (figure 1), using telehealth technology to enhance equitable access for research participants living in regional, rural or remote areas. The coordinating centre will be based at the Mater Research Institute-The University of Queensland in Brisbane. The study sites include Brisbane (metropolitan), Townsville (regional), Rockhampton (regional) and the Far North Queensland region including Cairns and Mareeba (regionals). In Brisbane, the partnering sites will be the Mater Mothers’ Hospital and Royal Brisbane Women’s Hospital, both quaternary maternity referral hospitals in Queensland. In Townsville, the study has partnered with the Aboriginal Community-Controlled Health Organisation (ACCHO), Townsville Aboriginal and Islander Health Service (TAIHS) and the Townsville University Hospital and Health Service for the protocol design. In Rockhampton, partnerships have been formed with Bidgerdii Community Health Service, Woorabinda Multipurpose Health Service and Central Queensland Hospital and Health Service. In Far North Queensland, the study has partnered with Wuchopperen Health Service, Mulungu Aboriginal Corporation Primary Health Care Service and Cairns and Hinterland Hospital and Health Service. It is likely that some smaller communities from within these regions may also take part once the study commences.

**Figure 1 F1:**
[figure not shown]
Proposed Strong Families Study sites across Queensland, Australia, with Brisbane as the coordinating centre.

### Patient and public involvement

This study was developed through extensive community consultation and co-designed by the Strong Families Indigenous Steering Committee (ISC). The committee identified major research themes relevant to their communities, which were informed by findings from a consultation-based study called The Indigenous Health Priorities Study (I-Priorities study).^30^,^34^ The formation of the ISC itself was a direct outcome of the I-Priorities study, wherein communities identified their research needs and priorities, and the research team built rapport and trust with Indigenous community-controlled health services. This study was facilitated with support from the Queensland Aboriginal and Islander Health Council (QAIHC).^30^ With this foundation in place, the ISC was formed in late 2023 and currently has 28 representatives from across Queensland, most of whom are Aboriginal and/or Torres Strait Islander. Members include Aboriginal community representatives and study champions from over 16 health services in Queensland, reflecting diverse cultural and professional knowledge, backgrounds and expertise. In-person co-design workshops, as well as quarterly online meetings, were held with the ISC from 2023 to 2026 to develop the SFS protocol, study design, data sovereignty and other key study elements.

Throughout these in-person workshops, the ISC strongly advocated for the integration of strength-based attributes across the study. For example, Indigenous data sovereignty, the use of Aboriginal health workers to deliver surveys and the incorporation of culturally responsive, strengths-focused tools and questionnaires that reflect resilience and cultural identity. It was emphasised that data analysis and interpretation of outcomes from the study should move beyond deficit-based narratives and instead highlight positive trajectories, strengths and holistic well-being of Indigenous families. SFS builds on the Indigenous Queensland Family Cohort (I-QFC), a feasibility study conducted in Brisbane as part of the broader longitudinal Queensland Family Cohort (QFC) study.^35^ I-QFC followed Indigenous families during pregnancy and the early postpartum period. These study findings were presented to the ISC and were used to guide and inform the design and data collection frameworks of SFS.

### Study governance

The SFS is jointly overseen by the Chief Executive Committee (CEC) and the ISC, ensuring Indigenous leadership and community representation. Senior Indigenous academics participate across both committees to ensure clear communication throughout the study. The ISC’s responsibilities encompass deliberation and decision-making to ensure Indigenous community input is integrated across all phases of the research process, including cultural oversight over the study. The CEC, comprised of research academics and representatives from partner organisations, is responsible for ensuring adherence to the project timeline and budget, implementation of protocols as well as interpretation and translation of findings. Both committees will convene at least quarterly and will be governed by Terms of Reference. The Terms of Reference will be reviewed annually by the ISC. Committee membership will be extended by invitation from current ISC members and the CEC, should any existing members need to step down. This will ensure that the ISC will remain active in a governance role over time. Any modifications to the SFS protocol and sub-study applications, including access to linked data, will be reviewed by the ISC before being submitted to the CEC and the appropriate ethics committee for approval.

### Study procedure

#### Study eligibility

Pregnant individuals who are less than 28 weeks of gestation and whose children may identify as Aboriginal and/or Torres Strait Islander, along with their partner (if applicable), will be eligible to participate in the study. To ensure the cohort is representative of the broader Queensland population, adoptive families, same-sex couples, single mothers or widowed mothers will also be invited to participate, including individuals with underlying health conditions. In many regions, English may not be the first language for Indigenous communities; however, due to the large number of Indigenous languages across Queensland, participation will be limited to individuals who can understand English. Exclusion criteria include participants under 16 years of age and those unable to provide informed consent.

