#### Recruitment

Initial recruitment will begin in Brisbane in mid-2026, followed by rollout to other sites shortly thereafter. Recruitment will be conducted through antenatal clinics at the listed study sites, employing a range of methods including flyers/posters, newsletters, social media and websites of partner organisations. Where feasible, experienced Indigenous health team members, such as midwives, Indigenous research assistants and Aboriginal health workers, will identify and approach potential pregnant individuals and their partners (if applicable).

Recruitment at hospitals will involve the screening of medical records to assess potential participants’ eligibility based on the study criteria, particularly that the mother is carrying an Indigenous infant in her pregnancy. This process will also ensure care is taken not to contact individuals who may have recently experienced an unexpected or adverse pregnancy complication, eg, miscarriage, stillbirth, termination or fertility issues, as this could trigger discomfort or emotional distress. Potential participants will be contacted either face-to-face, via phone or email. Those who express interest in the SFS will receive a Participant Information Sheet and Consent Form (PICF), along with a link to access the SFS Participant Information Video. An Indigenous member of the study staff will then arrange to discuss the study in detail and address any questions, preferably in a face-to-face setting. Potential participants will be advised that participation in the study is entirely voluntary, and individuals can withdraw at any time. The consent process will also explain the nested family support programmes, and parents will have the option to self-refer at any time and allow data linkage with SFS. The written consent of the pregnant participant will include the consent of her infant/young child. Parental/guardian consent may be sought from some young participants (between 16 and 18 years) if deemed necessary by the research team, but only when the youth provides verbal consent to participate in the study. Consent will be obtained in a culturally sensitive manner, including the use of a Participant Information Video recorded by ISC members and the study team, prepared using accessible language to support potential participants who may appreciate support in understanding the complexity of the study.

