#### Study regimen

Data will be collected at multiple points throughout the study (figure 2, online supplemental table 1): < 28 weeks gestation, ≥ 28 weeks gestation, at the time of delivery, during the post-delivery period (in the hospital ward), at 6 weeks postpartum and at regular intervals throughout early childhood (from 3 to 36 months CA). Follow-up assessments will continue annually through early childhood.

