##### Statistical analysis

To examine relationships between perinatal strengths/risk factors and continuous outcomes (eg, Kimberley Mum's Mood Scale (KMMS)), we will use linear or mixed effects regression for repeated measures. Binary outcomes will be analysed using logistic regression, and count outcomes with Poisson or other suitable count models. Analyses will account for the multi-site teletrial design by adjusting for clustering at the site/community level (eg, through random or fixed effects or robust standard errors). For multivariable modelling, candidate predictors will be screened individually, with final model selection guided by Bayesian Information Criteria. Model calibration will be checked graphically, and internal validation performed via bootstrap resampling.

Missing data will be treated case-by-case using multiple imputation when data are plausibly missing at random, and pattern mixture methods with sensitivity analyses when not missing at random mechanisms are likely. Longitudinal mixed-effects models will use all available observations under missing at random assumptions. If differential loss to follow-up occurs, we will apply weighting-based sensitivity analyses (eg, inverse probability of follow-up weighting). Each analysis will include appropriate adjustments for multiple comparisons to balance type I and II error risks.

For the PACT Online and LEAP programmes, effectiveness will be investigated using mixed effects models with programme participation included as the main effect and models adjusted for baseline factors. Differences in characteristics of families who do and do not participate in the programmes will be assessed. If any differences exist, they will be adjusted for in analyses using weighting methods such as propensity matching. Cohort embedded summaries of eligibility, referral and uptake will be reported descriptively. The sensitivity of observational comparisons (eg, uptake vs non-uptake) will be assessed.

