The collection of biological samples represents a unique aspect of the study. To the best of our knowledge, this will be the first birth cohort study to collect and analyse such biological parameters within the two-parent-and-child triad across multiple regions in the state of Queensland. This novel component provides valuable opportunities to better understand the interplay between biological, environmental and social determinants of health, offering deeper insights into the health trajectories of Indigenous families.

There are several potential limitations of the study. As with other longitudinal studies, the Strong Families Study involves significant time and resource investment for its rigorous design and implementation. For participants, particularly those with young children, the requirement for multiple in-person visits to the study site could be burdensome. This may lead to fatigue or disengagement, thereby impacting participant retention and data consistency over time. Moreover, the need for consistency in data collection, delivery of yarning scripts, health education delivery and adherence to the study protocol across different locations requires careful planning and resource allocation. The study has proactively established a rigorous implementation and evaluation process using the RE-AIM framework.^41^ By implementing these processes, the study aims to mitigate potential challenges, adapt study procedures to the unique contexts of each community and enhance the overall rigour and reliability of the research outcomes. A further limitation is the restriction of participant enrolment to individuals who are <28 weeks gestation. This criterion may exclude late presenters, potentially reducing the generalisability of the findings to the broader population.

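### For outcomes possible before 28 weeks, gestation at entry should be fixed in the analysis; otherwise factors linked to early booking can look harmful with no true effect

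*Protocol article*

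**What the plan says.** All references are to the Protocol article.

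- **Entry.** "Study eligibility" admits "Pregnant individuals who are less than 28 weeks of gestation" and sets no earliest week. "Recruitment" adds "Recruitment will be conducted through antenatal clinics at the listed study sites", and staff take care "not to contact individuals who may have recently experienced an unexpected or adverse pregnancy complication". That care is plainly right. Its consequence for the analysis is that events before contact never enter the data.
- **Outcomes.** The Introduction lists the outcome domains as "1) maternal pregnancy outcomes, (2) neonatal and birth outcomes and (3) early childhood developmental outcomes".
- **Model.** "Statistical analysis" states "Binary outcomes will be analysed using logistic regression". Candidate predictors are screened one at a time and the final model is guided by BIC. No time origin is given, and gestation at entry is not mentioned.
- **Weighting.** The only weighting for incomplete observation concerns the period after entry: "If differential loss to follow-up occurs, we will apply weighting-based sensitivity analyses".
- **Visits.** "Study regimen" places the first collections at "< 28 weeks gestation, ≥ 28 weeks gestation, at the time of delivery".
- **Limitation.** For the 28-week rule the Discussion gives one: "This criterion may exclude late presenters, potentially reducing the generalisability of the findings to the broader population". That concerns generalisability, not comparisons within the cohort.

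**The concern.** A family enrolled at week 10 can contribute a loss or birth at week 15 or week 22. A family enrolled at week 27 cannot, because its pregnancy had to last to week 27 before it could join. A logistic model that ignores week of entry treats the two as having had the same opportunity for the event.

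If an exposure is associated with booking early, the exposed group is observed for longer before 28 weeks and collects more early events, even when the exposure does nothing. Culturally safe pregnancy care and social determinants of health are among the study's themes and could plausibly be related to booking time. For these outcomes the error would make a strength look like a risk, in a study that sets out to identify strengths. A larger sample would not reduce it.

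The second antenatal visit raises a related issue. Its measurements exist only for pregnancies that lasted to that visit, so relating them to earlier events, or to births that came first, would use data that are missing because of the outcome.

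**Working it through.** **The plan's own figures.** The article gives none on this point. Its 80% power figure concerns the neurodevelopmental outcome. It reproduces (5% v 13%, 200 per group, two-sided 0.05: power 0.80) and is not affected.

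**Why gestation at entry can drop out.** BIC keeps a covariate only if twice the log-likelihood rises by more than ln(n). With n = 400 that is ln(400) = 5.99. With few events, a variable that matters for bias can fail this test, and it may not be a candidate at all.

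**Set-up.** All rates, entry weeks and mixes below are assumptions. Two groups of 200 have the same true risk. In the exposed group 70% enter early and 30% late; in the unexposed group 30% and 70%. With R(w) the risk of loss or birth from week w to 28:

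- exposed risk = 0.7·R(early) + 0.3·R(late)
- unexposed risk = 0.3·R(early) + 0.7·R(late)
- composite with a further 12% births at 28–36 weeks: p + (1 − p)·0.12

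**Scenario A: even hazard, entry at week 14 or 26.** Let r be the risk over weeks 12–28. Then h = −ln(1 − r)/16 and R(w) = 1 − exp(−h(28 − w)).

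| r | R(14) | R(26) | Exposed v unexposed | Risk ratio | Events | Composite | Risk ratio |
|---|---|---|---|---|---|---|---|
| 1% | 0.88% | 0.13% | 0.65% v 0.35% | 1.86 | 1.3 v 0.7 | 12.57% v 12.31% | 1.02 |
| 2% | 1.75% | 0.25% | 1.30% v 0.70% | 1.85 | 2.6 v 1.4 | 13.15% v 12.62% | 1.04 |
| 3% | 2.63% | 0.38% | 1.95% v 1.06% | 1.85 | 3.9 v 2.1 | 13.72% v 12.93% | 1.06 |

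The standard error of the composite log risk ratio is √[(1 − p₁)/(200p₁) + (1 − p₂)/(200p₂)], about 0.26. The bias on that scale is 0.02 to 0.06.

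**Scenario B: early losses included, entry at week 10 or 20.** Loss over weeks 8–20 is 3%, 5% or 10%, with the weekly hazard falling by a quarter each week. Loss or birth over weeks 20–28 is 1%, 1.5% or 2%. The share of the week 8–20 hazard still to come at week 10 is (0.75² − 0.75¹²)/(1 − 0.75¹²) = 0.548. For the first row, R(10) = 1 − exp(0.548 × ln 0.97) × 0.99 = 2.64%.

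| R(10) | R(20) | Exposed v unexposed | Odds ratio | Events | Nominal 5% test rejects | Composite odds ratio |
|---|---|---|---|---|---|---|
| 2.64% | 1.0% | 2.15% v 1.49% | 1.45 | 4.3 v 3.0 | 7% | 1.05 |
| 4.23% | 1.5% | 3.41% v 2.32% | 1.49 | 6.8 v 4.6 | 10% | 1.08 |
| 7.50% | 2.0% | 5.85% v 3.65% | 1.64 | 11.7 v 7.3 | 18% | 1.15 |

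**Outcomes after 28 weeks.** Everyone has entered by then. Among pregnancies reaching 28 weeks, both groups have the same 12% risk of birth at 28–36 weeks: odds ratio 1.00.

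**With conditioning.** Within one entry week the two groups have the same R(w), so the ratio for early events returns to 1.00.

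**Second visit.** Again assume 12% births at 28–36 weeks. With an even hazard, the remaining risk before 37 weeks is 10.7% after a visit at week 29 and 4.2% after one at week 34 (ratio 2.6). With three-quarters of the hazard in weeks 34–36 it is 11.5% v 9.1% (ratio 1.3). For second-visit exposures, delayed entry therefore reaches ordinary preterm birth.

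**The case against.** The case against is substantial, and most of it limits the point.

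- **Time origin.** A reader might infer that outcomes are analysed from enrolment. The article does not say so; it gives no time origin.
- **Named outcomes.** A reader might infer that pregnancy loss or preterm birth is a planned endpoint. Neither is named as one. Miscarriage and stillbirth appear only as reasons not to contact people. The point is therefore conditional on such outcomes being analysed under the pregnancy and birth aims.
- **Scope.** It is tempting to read the bias across all of aims 1 and 2. That fails: after 28 weeks there is no unequal time at risk with first-visit exposures. Selection through survival to entry may remain, but it has no fixed direction.
- **Size.** Comparing a group that all enters at week 14 with one that all enters at week 26 gives a ratio of about 7 (2.63% v 0.38%). No real exposure separates families so completely. A 70/30 mix brings it to about 1.85, on 2 to 6 events in total.
- **Link to exposure.** Entry week also reflects when staff reach a family, so its association with the exposures is plausible rather than documented.
- **Second visit.** The article nowhere proposes relating second-visit exposures to earlier events, and visit windows may be in the figure or supplement not shown.
- **Unseen detail.** Covariates and risk sets are commonly left to a full protocol or analysis plan. That stands for detail. But the article does commit to a model class and a selection rule for binary outcomes, and that rule can omit gestation at entry. It also discusses the weakness of the entry rule and mentions only generalisability.

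**Conclusion.** The point holds in a narrow form. If an outcome that can occur before 28 weeks is analysed under the stated model and selection rule, a null factor associated with early booking can look harmful. The direction follows from the entry rule together with that association; the size depends on assumptions. Under the two scenarios the spurious ratio is about 1.5 to 1.9 for events before 28 weeks, on roughly 2 to 19 events among 400 families, and about 1.02 to 1.15 for a composite of loss or any preterm birth. In the even-hazard scenario the composite bias is small beside its standard error.

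The documents do not support the wider conclusion that pregnancy and birth outcomes are biased as a whole, or that the primary outcome or the sample size is compromised. This is an inexpensive improvement to the analysis wording, not a flaw in the cohort's design.

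**What to change.** In "Statistical analysis":

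1. For outcomes that can occur before 28 weeks, state the time origin and always condition on gestation at entry. Use time-to-event models on the gestational-age scale with delayed entry at each family's gestation at enrolment. Where events are too few for that, force gestation at entry into the logistic model, outside BIC selection.
2. Otherwise, define birth outcomes among pregnancies reaching 28 weeks, where logistic regression needs no change for this reason.
3. Use first-visit exposures as the main exposures for aims 1 and 2. Relate second-visit exposures only to events after that visit, with entry at that visit's gestation.

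In the Discussion, add delayed entry to the limitation on the 28-week rule.

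Cost: wording only. Gestation at entry is already needed for eligibility, and recruitment, visits and sample size are unchanged. The price is hazard ratios or one extra covariate for these outcomes, and second-visit exposures not being used for earlier events.
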